## Methods

### Overview

In this stage 0 (of the NIH Stage Model for behavioral intervention development) study, we propose an interdisciplinary mixed method approach to examine the occurrence of daily stressors in the moment they occur for midlife adults in the built and natural environment using mobile and wearable technology. A total of 150 midlife adults will be enrolled in this study on a rolling basis for 3-week periods. Participants will meet with a researcher in person at the start and end of their 3-week study period. They will be provided with a smartphone preloaded with the STRIVE app and a Polar Unite smartwatch. They will be instructed to carry the phone and wear the watch for the 3-week duration of the study. Each enrolled participant will use one or more daily stress measurement tools in any given week, randomized to account for participant priming. In 1 week of participation, participants will complete the DISE by the Research Electronic Data Capture (REDCap; Vanderbilt University) survey every evening. In another week of participation, participants will use the STRIVE app to report daily stressors in real time and complete the DISE every evening. In another week of participation, participants will only report stressors in real time through the STRIVE app. Automated SMS text messages will be sent to participants each day to remind them of what they need to do to remain active in the study and provide survey links when needed.

Participants will be recruited from the greater Indianapolis area in Indiana. As those in underrepresented minority groups and low-income areas have previously been found to experience greater levels of stress, we will use stratified sampling to obtain a sample that is racially and socioeconomically diverse (Table 1). Income levels are defined as the bottom, middle, and top third of household incomes based on 2020 US Census percentiles (low income: <US $39,535; middle income: US $39,535-$85,076; high income: >US $85,076) [32]. Participants will be recruited with the assistance of the Indiana Clinical and Translational Sciences Institute recruitment concierge services and their community partnerships. Recruitment materials will be posted on community-based social media pages, on paper flyers in public community spaces, and through all communication channels operated by community health partners.

**Table 1 table1:** Study sample stratified by race and household income (N=150).

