**Figure 1 figure1:**
[figure not shown]
The Stress Reports in Variable Environments (STRIVE) app.

We have created a protocol to promote the safety of research participants during their reporting of daily stressors with the STRIVE app. If they cognitively appraise themselves as stressed and are in a situation in which it is unsafe to use their phones (eg, driving a car), they are asked to proceed to the nearest safe location before recording their experience. Participants will be asked to indicate when and where the stressor occurred if they are not reporting from the location in which the stress occurred in their later description of it. Many people go through a day without experiencing a stressor [43]; for days when this is the case, participants will be asked to indicate on their app that they had not experienced stress but were still actively participating in the study.

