### Comparison of STRIVE and DISE Stressor Data

We will compare the number of stressors reported, the type of stressors reported, and the subjective severity of stressors reported by the same individual using the DISE and STRIVE app across 3 time periods. The 3 time periods are designed to differentiate between stand-alone use of each instrument and concurrent use of both instruments, as there is potential for these instruments to be complementary in terms of the scope and depth of data captured. Thematic coding of stressors reported through the DISE and STRIVE app will be conducted to allow for comparison between the two. All stressors will be coded into 7 categories specified by the DISE to retain consistency. Stressful events are categorized into 1 of 7 broad classifications organized by interpersonal tensions, work or education, home, finances, health or accident, network, and miscellaneous. As the unit of analysis of the DISE is the “day,” we will conduct a repeated measures ANOVA to compare the number of stressors reported per day, the average subjective severity of stressors per day, and the type of stressors reported per day across the 3 modes of daily stress reporting, including an interaction of group (STRIVE or DISE) and mode (using only one or both together) to test if there is any effect on the reported stressors by use. A factor will also be included for the order receiving the conditions to account for carryover effects. Models will also be adjusted by demographic variables.

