## Results

This study will take approximately 24 months to complete and will take place between December 2022 and November 2024. Enrollment began in August 2023 and is expected to be completed by July 2024. We expect the following study findings:

A better understanding of where and when stressors occur for midlife adults in free-living conditions. We hypothesize that the quantity of stressors reported, type of stressors reported, and subjective severity of stressors reported by midlife adults will differ by location (eg, at home vs at a park) and time (eg, morning vs evening) throughout the built and natural environment.An understanding of specific elements of the built and natural environment that contribute to midlife adults’ daily stress. We hypothesize that distinct environmental characteristics (eg, abandoned buildings) will emerge as contributors to stress through the qualitative analysis of stressor descriptions and pictures of stressful environments.An understanding of how the STRIVE-based EMA of daily stress is supplementary or complementary to the DISE. We hypothesize that, when reporting through the STRIVE app compared with when reporting through the DISE, midlife adults will report a greater number of daily stressors, a lower average stressor severity, and different types of stressors.

Throughout the study, we will present our research findings at relevant academic or professional conferences and publish peer-reviewed papers. We will also share our study findings with partner governmental organizations and nongovernmental organizations in the state of Indiana. These organizations will likely find our data useful for future community planning.

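### Stressor type is an unordered 7-category label assigned to a repeated measures ANOVA with no numeric daily score; if scored as daily counts per category, a difference in mix is not separated from a difference in total

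*Protocol article*

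**What the plan says.** The section on comparing STRIVE and DISE data in the protocol article first defines the outcome: "All stressors will be coded into 7 categories specified by the DISE to retain consistency". The categories are nominal: "Stressful events are categorized into 1 of 7 broad classifications organized by interpersonal tensions, work or education, home, finances, health or accident, network, and miscellaneous".

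The same section takes the day as the unit of analysis and names one method for all three outcomes: "we will conduct a repeated measures ANOVA to compare the number of stressors reported per day", followed by average severity per day and "the type of stressors reported per day across the 3 modes of daily stress reporting". The model is to contain an interaction of instrument (STRIVE or DISE) with mode of use (alone or together), a factor for order, and demographic variables. The section gives no count, indicator, share or other score for type, and names no categorical model.

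The Results section states the matching hypothesis for STRIVE relative to DISE: "midlife adults will report a greater number of daily stressors, a lower average stressor severity, and different types of stressors".

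**The concern.** Number per day and average severity per day are numeric, and an ANOVA can be fitted to them. Type is a label with no order, mean or variance, so an ANOVA is not defined for it until someone supplies a numeric score. The article names the method without the score.

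The choice of score matters because the study predicts a higher total under STRIVE. If type is scored as daily counts per category, a tool that catches more of everything in the same proportions has a higher expected count in every category. A finding of different types could then only restate the finding of more stressors. At stake is one of the three parts of the STRIVE versus DISE hypothesis. If the score is chosen after the data are seen, the reader cannot tell which question was answered.

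**Working it through.** The article states no alpha, effect size or power for this comparison, so there is no figure of its own to reproduce.

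**Inputs from the article.** 150 participants, each using all three reporting modes for a week (Overview); 7 unordered categories, the day as unit, repeated measures ANOVA (comparison section); a greater number predicted under STRIVE (Results).

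**Assumptions, not in the article.** Two-sided alpha 0.05; a DISE total of 0.5 to 1.0 stressors per day; the category mix; the ratio k of the STRIVE total to the DISE total. Only the two stand-alone weeks are simulated.

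**Step 1: expected counts.** Let the DISE total be T per day and let category c have share s(c) under both tools. The expected daily counts are T·s(c) for DISE and k·T·s(c) for STRIVE, so the difference is (k − 1)·T·s(c). This is above zero for every category when k > 1, although the mix is identical. With T = 1.0 and k = 1.25:
- a category with share 0.28 goes from 0.28 to 0.35 per day, a difference of 0.07;
- a category with share 0.08 goes from 0.08 to 0.10 per day, a difference of 0.02;
- the STRIVE shares are 0.35/1.25 = 0.28 and 0.10/1.25 = 0.08, unchanged.

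**Step 2: instrument-by-category test on counts.** This tests whether the differences are equal across categories. Here 0.07 − 0.02 = 0.05, so it detects something although the mix is the same. If all seven shares are 1/7, each difference is 0.25/7 = 0.036 and the contrast is zero. The test is therefore inflated only when categories differ in frequency.

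**Step 3: how often a false difference in type appears.** Two simulations with the same true mix under both tools, 150 people and 7 days per tool:
- A: gamma-Poisson counts, person frailty shape 1, week-level variance 0.2, shares .25/.25/.20/.08/.07/.08/.07.
- B: Poisson counts, between-person log-SD 0.6, shares 28/22/18/8/8/8/8% or all equal, 1,000 runs per setting.

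| k | At least one of 7 categories, unadjusted | At least one, Bonferroni | Instrument-by-category on counts, unequal mix |
|---|---|---|---|
| 1.0 | A 28–29%; B 29–32% | B 4–5% | B 5% |
| 1.1 | B 48–62% | A 7–13%; B 11–20% | B 7–10% |
| 1.25 | A 78–86%; B 91–99% | A 38–57%; B 51–89% | A 15–22%; B 21–42% |
| 1.5 | A over 99%; B 100% | B 99–100% | A 57–79%; B 71–96% |

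The Bonferroni figures for A come from a repeat of that set-up with 600 runs per setting, in which the unadjusted rate at 1.25 was 82–90%. With an equal mix, B's instrument-by-category test stayed at 4–7% for every k.

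**Step 4: separating multiplicity from confounding.** Seven independent unadjusted tests give 1 − 0.95^7 = 0.30, which explains the row for k = 1.0. The unadjusted column thus combines two problems. The Bonferroni column isolates the one raised here: about 5% at equal totals, rising with k.

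**Step 5: a test of composition.** On the same kind of data, a test of shares that allows for the total gave 4–5% in A and 3.5–6.5% in B, for k up to 1.5 and 2.0 respectively. Shares need a stressor to be defined. On a day with none, the daily share is 0/0, and the STRIVE app section says "Many people go through a day without experiencing a stressor". The composition has to be taken over a longer period or conditional on a reported stressor.

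**The case against.** The best defence is that the outcome is described per day. A day can hold several stressors or none, so some derived quantity must be intended: a count or yes/no per category, a share, or the number of distinct types. On this view the score is only unstated and may be in an analysis plan not shown. It stands that the text does not prescribe counts and that other scores exist. It does not clear the text, which names a method that fits the outcome only after a step it omits, and the possible scores answer different questions.

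A second defence is that the hypothesis speaks of different types, not of a different mix given the total. The section asks whether the tools complement each other in scope and depth, and which categories one tool captures more often per day is a fair question. That also stands. Category frequencies may be reported, provided that they are not read as mix.

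A reader might infer more than the article supports. It does not commit the study to seven unadjusted tests, so the roughly 30% false-positive rate at equal totals is not a property of the plan. Nor will a false difference appear whenever STRIVE records more, or in every category. At a 1.1-fold total the adjusted rate is 7% to 20%, and at 1.5-fold B found on average 4.9 to 6.8 of the 7 categories significant without adjustment.

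**Conclusion.** The point holds in a limited form. The article assigns a repeated measures ANOVA to an unordered label without defining a score. Under one natural score, daily counts per category, a difference in type is confounded with the greater number that the study itself expects. With Bonferroni adjustment and no true difference in mix, the chance of a false difference is roughly 7% to 20% at a 1.1-fold total and 38% to 89% at 1.25-fold. These figures rest on assumed rates, mix, ratio and alpha. The direction for the category tests follows from Step 1 and does not depend on them. The instrument-by-category test is affected only if categories differ in frequency.

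This should be fixed, but it is not a defect that invalidates the study. It concerns one of three parts of the third aim in a stage 0 study. This objection leaves the number and severity comparisons, the design and the data collection untouched.

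**What to change.** Take type out of the repeated measures ANOVA. Analyse the category of each reported stressor with a multinomial mixed model with person random effects, or an equivalent person-clustered test. Keep the planned terms: instrument, mode (alone or concurrent), their interaction, order, and demographic variables.

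Use one joint test of instrument on the category shares, with 7 − 1 = 6 degrees of freedom. Because the interaction stays in the model, say whether this test refers to stand-alone use or to the average over both modes. Report the seven share differences with intervals, and read single categories only after a positive joint test or with Holm adjustment. Daily frequencies per category may be reported alongside, labelled as frequency and not as mix.

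The cost is a change of analysis wording and a little programming, with no new data. The unit for this outcome moves from the day to the reported stressor, which the text should say, and rare categories may have to be merged, which would reduce the degrees of freedom.

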In response to this research gap, we propose to use our novel custom-built Stress Reports in Variable Environments (STRIVE) ecological momentary assessment (EMA) mobile phone app to measure the experience of daily stress of midlife adults in free-living conditions. Using our app to capture data in real time will allow us to determine (1) where and when daily stress occurs for midlife adults, (2) whether midlife adults’ daily stressors are linked to certain elements of the built and natural environment, and (3) how EMA measurement of daily stress is similar to and different from a modified version of the popular Daily Inventory of Stressful Events (DISE) measurement tool that captures end-of-day stress reports (used in the Midlife in the United States [MIDUS] survey) [31].

Completing this study will expand our understanding of mid-life adults’ experience of stress in free-living conditions and pave the way for data-driven individual and community-based intervention designs to promote health and well-being in midlife adults. Potential interventions that could stem from our data include technology-based “just-in-time” interventions that account for spatiotemporal location, mindfulness-based interventions that incorporate environmental stress triggers, and community-based interventions designed to eliminate environmental stressors that are commonly experienced by midlife adults (eg, congested areas).

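### The STRIVE–DISE comparison gives mode three levels and then two, leaves a concurrent day's two reports unlinked, and compares daily means that cannot show whether the tools are similar or complementary

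*Protocol article*

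**What the plan says.** The Overview in the protocol article's Methods gives each participant three weeks in randomized order:

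- a DISE week: "In 1 week of participation, participants will complete the DISE" by evening survey;
- a concurrent week: "participants will use the STRIVE app to report daily stressors in real time and complete the DISE every evening";
- a STRIVE week: "participants will only report stressors in real time through the STRIVE app".

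The section Comparison of STRIVE and DISE Stressor Data fixes the analysis: "As the unit of analysis of the DISE is the “day,” we will conduct a repeated measures ANOVA". The outcomes are the number, average severity and type of stressors per day, compared "across the 3 modes of daily stress reporting". The same sentence adds the interaction: "including an interaction of group (STRIVE or DISE) and mode (using only one or both together"). A factor for order and demographic adjustment are also planned. Stressors from both tools are to be coded into the same 7 DISE categories.

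The third aim in the Introduction is to learn "how EMA measurement of daily stress is similar to and different from a modified version" of the DISE. The comparison section justifies the concurrent week by the possibility that the tools complement each other. The Results section expects to learn whether STRIVE is supplementary or complementary to the DISE. Its hypotheses are about differences: more stressors, lower average severity and different types with STRIVE.

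**The concern.** There are three linked difficulties.

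1. **Factor structure.** A three-level mode factor and a two-by-two crossing of instrument with use are different models. Which one applies depends on whether a concurrent day contributes one record or two, and the article does not say.
2. **Dependence.** If a concurrent day contributes two records, both describe the same day's stress in the same person. The article names the day as the unit but no term or error structure that links them.
3. **Match to the aim.** The only quantitative method stated compares per-day summaries between modes. Whether two tools overlap or complement each other depends on what each catches on the same day.

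The test of whether joint use changes reporting, and the study's answer to its third aim, are at stake.

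**Working it through.** The article states no alpha, power or effect size for this comparison, so there is no figure to reproduce. The inputs are the three week types and 7-day weeks (Overview), N = 150 (Overview), and the two definitions of mode (comparison section). The same-day correlation is not given and is assumed below.

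**Step 1: which layout supports the interaction.** Code instrument g = +½ (STRIVE) or −½ (DISE), and use m = −½ (alone) or +½ (concurrent). The model is intercept + g + m + g×m, with 4 parameters.

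| Layout | Cells | Rank | Interaction estimable |
|---|---|---|---|
| Concurrent week as one pooled record per day | 3 | 3 of 4 | no |
| Concurrent week, one instrument kept | 3 | 3 of 4 | no |
| Concurrent week, one record per instrument | 4 | 4 of 4 | yes |

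Put another way, three condition means carry 2 degrees of freedom, while instrument, use and their interaction need 1 + 1 + 1 = 3. The Overview shows that both tools report separately in the concurrent week, so all four cells are observed. Each participant then has up to 7 + 7 + 14 = 28 records.

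**Step 2: what the same-day link does to standard errors.** Let ρ be the share of day-level (within-person) variance common to the two reports of one concurrent day. The ratio of the true standard error to one that treats the records as independent within person is:

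- STRIVE minus DISE in the concurrent week: √(1 − ρ)
- interaction: √((2(1 − ρ) + 2)/4)
- use (alone versus concurrent) main effect: √((2 + ρ)/2)

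| ρ (assumed) | Concurrent difference | Interaction | Use effect |
|---|---|---|---|
| 0.2 | 0.89 | 0.95 | 1.05 |
| 0.4 | 0.77 | 0.89 | 1.10 |
| 0.6 | 0.63 | 0.84 | 1.14 |
| 0.8 | 0.45 | 0.77 | 1.18 |

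Inverting the first column, 1/√(1 − ρ) runs from 1.12 (ρ = 0.2) through 1.58 (ρ = 0.6) to 2.24 (ρ = 0.8). This is how far the standard error of the instrument difference is overstated.

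**Step 3: effect on a nominal 5% test.** With ratio k, the actual level is about 2[1 − Φ(1.96/k)]. At ρ = 0.2, 0.6 and 0.8 this gives about 6%, 9% and 10% for the use effect, and about 4%, 2% and 1% for the interaction.

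A simulation (150 participants, 7 days per week, 4,000 runs) analysed person-by-cell means in two ways:

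| Analysis of cell means | Use effect, ρ = 0.2 / 0.6 / 0.8 | Interaction, ρ = 0.2 / 0.6 / 0.8 |
|---|---|---|
| Person term, one pooled error | 6.6% / 10.5% / 12.4% | 3.9% / 2.5% / 2.0% |
| Two-way within-subject ANOVA, separate error per effect | 4.9% / 4.7% / 5.2% | 4.6% / 5.2% / 5.3% |

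The first row differs slightly from the day-level arithmetic because the pooled residual is itself smaller when taken over four cell means. The second row holds its level.

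**Step 4: what means can and cannot show.** Suppose each tool records two stressors on every concurrent day. The daily means are equal if both catch the same two, and equal if they catch four different ones. The same holds within a category: equal category frequencies do not show that the tools caught that category on the same days. The concurrent week is the only one in which both tools cover the same days, giving up to 150 × 7 = 1,050 same-day pairs.

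**The case against.** A reader might infer from the three-level wording that the interaction cannot be estimated at all. The documents do not support that. The interaction clause itself describes a two-by-two layout, and the Overview shows that every cell is filled. Nothing says that the two concurrent reports will be merged.

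A reader might also take the standard-error factors as errors in the plan. They are not. They apply only to a model with one pooled error, which the article does not state, and they rest on an assumed correlation. The article does say that the comparison is within the same individual, and a within-subject ANOVA on cell means with effect-specific errors handles the correlation between the two concurrent cells. An article may leave the error structure to a fuller plan.

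On agreement, the stated hypotheses concern differences, for which mean comparisons are suitable. The common 7-category coding goes some way towards comparing content. The article nowhere proposes to read similarity from a non-significant test.

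These objections remove the claim of non-identifiability and any claim that the analysis is bound to be wrong. They do not settle which definition of mode applies. The effect-specific ANOVA needs the four cells that the text leaves undefined, and the text sets the day as the unit without mentioning cell means. Nor do they close the gap on the aim: the directional hypotheses cover how the tools differ, while the Introduction and Results also ask about similarity and complementarity.

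**Conclusion.** The point holds as an inconsistency in the stated model and a partial mismatch between the third aim and its stated analysis. The design itself is sound on this point.

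- The two definitions of mode must be reconciled. This is certain from the text and needs no assumption.
- The link between same-day reports is unstated. If it were ignored in a day-level model with one pooled error, the instrument difference and the interaction would be tested conservatively and the use effect anti-conservatively. The sizes in the working depend on the assumed range of 0.2 to 0.8 for the same-day correlation, and on there being no other person-level variance components.
- Daily means alone cannot show whether the tools are similar or complementary. The concurrent week already supplies the data that can.

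**What to change.** In Comparison of STRIVE and DISE Stressor Data:

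1. Replace the two uses of mode with four within-person cells: instrument (STRIVE, DISE) by use (alone, concurrent).
2. State that each concurrent day gives two linked records, one per instrument.
3. Specify either random effects for participant and participant-day, or a within-subject ANOVA with a separate error for each effect. A participant-week term is worth considering with the random effects, since each condition occupies one week.
4. Add a paired same-day analysis of the concurrent week. Report agreement for count and for severity (limits of agreement or an intraclass correlation). For each of the 7 categories, report the shares of days caught by STRIVE only, by the DISE only and by both. Severity pairs will be fewer than 1,050, because average severity exists only on days when a stressor was reported in each tool.
5. Base statements about similarity or complementarity on item 4, with a caveat: reporting in the app by day may prime that evening's DISE, so concurrent-week agreement may not represent either tool used alone.

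The cost is a few sentences and modest extra programming. No new data or visits are needed, and the 7-category coding is already planned.

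### The order factor, as described, does not adjust the within-person STRIVE versus DISE contrast for carryover; the contrast is biased only if priming differs between the two stand-alone weeks

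*Protocol article*

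**What the plan says.** The Overview describes three one-week conditions per participant: DISE only, STRIVE only, and a combined week ("In another week of participation, participants will use the STRIVE app to report daily stressors in real time and complete the DISE every evening"). Allocation of tools to weeks is "randomized to account for participant priming". The set of orders, their balance and any gap between weeks are not given. The sample is 150 people, each followed for three weeks.

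The section Comparison of STRIVE and DISE Stressor Data compares reports "by the same individual using the DISE and STRIVE app across 3 time periods" and states that "we will conduct a repeated measures ANOVA to compare the number of stressors reported per day", along with average severity and type of stressor. The only interaction it names is instrument (STRIVE or DISE) by mode (alone or together). It then adds: "A factor will also be included for the order receiving the conditions to account for carryover effects". The same section says the three periods are meant to separate stand-alone use of each instrument from concurrent use.

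**The concern.** The article names a model term and gives it a job. The comparison is within person, while the order of conditions does not vary within a person, so the term works between people and has no hold on the contrast of interest.

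This matters because the article itself expects priming. Each instrument is in use in two of the three weeks, and no washout is described. A DISE-only week is free of earlier STRIVE use only when it comes first, and the same is true of a STRIVE-only week and earlier DISE use. The third hypothesis in Results (more stressors, lower average severity and different types with STRIVE) rests on this contrast. With the stated term, the published estimate could be presented as adjusted for carryover when it is numerically the unadjusted one.

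**Working it through.** The article gives no carryover size, effect size or power figure, so there is nothing of its own to reproduce.

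**Inputs.** From the article: 150 participants, 3 weeks, 3 conditions, within-person comparison. Assumed: all 6 orders used equally (25 people each), a true STRIVE minus DISE difference of 0.30 stressors per day, and the priming sizes below.

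**Step 1: exposure.** Write D, S and B for DISE only, STRIVE only and both. The orders are DSB, DBS, SDB, SBD, BDS, BSD. D comes first in 2 of 6 orders, so 2/6 × 150 = 50 people have a STRIVE-naive DISE-only week. The other 4/6 (100 people) have had STRIVE earlier, because both S and B include it. By symmetry, 100 of the 150 STRIVE-only weeks follow DISE use.

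**Step 2: the order factor.** Each participant's contrast is (mean in S week) − (mean in D week). A term that is constant within the participant adds the same amount to both and drops out. Week position does not help either: with balanced orders each condition occurs equally often in each week, so a week term is orthogonal to condition.

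**Step 3: bias under two mechanisms.**

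- *Carryover from the preceding week only.* Let λ be what a condition leaves behind. S follows D in 2 orders and B in 2, giving a mean of (λ_D + λ_B)/3. D follows S in 2 and B in 2, giving (λ_S + λ_B)/3. Bias = (λ_D − λ_S)/3.
- *Any earlier week primes a stand-alone week.* Let π_D and π_S be the shifts in D and S weeks after week 1. Each applies in 4 of 6 orders. Bias = (2/3)(π_S − π_D).

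**Step 4: numbers for the second mechanism, true difference 0.30.**

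| π_D | π_S | Bias | Estimate, no adjustment | With order factor | With week |
|---|---|---|---|---|---|
| 0.30 | 0 | (2/3)(−0.30) = −0.20 | 0.10 | 0.10 | 0.10 |
| 0.30 | 0.15 | (2/3)(−0.15) = −0.10 | 0.20 | 0.20 | 0.20 |
| 0.30 | 0.30 | 0 | 0.30 | 0.30 | 0.30 |

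Noise-free least squares on the 150-person layout gives these same values. For the first mechanism, carryover of 0.30 left only by DISE gives 0.30 + 0.30/3 = 0.40. If only STRIVE leaves it, the estimate is 0.30 − 0.30/3 = 0.20. The bias can therefore go either way.

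**Step 5: other sets of orders.** With 3 cyclic orders of 50 people, the bias per unit of carryover ranged from −0.667 to +0.667 over the scenarios tried, and was 0 in some. With simple randomization of 150 people to 6 orders, equal carryover gave a mean bias of about 0 (SD 0.07 per unit).

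**Step 6: what modelling it costs.** Let σ_w² be the within-person variance of a weekly mean. The plain contrast has variance 2σ_w²/150 = 0.0133σ_w². Adding week and a prior-exposure term for each stand-alone condition returns 0.30 in every row of the table, but the variance becomes 0.0667σ_w². That is 5 times as large, so the standard error grows by √5 ≈ 2.2. With a term for DISE-only weeks alone the variance is 0.0533σ_w² (4 times), and the equal-priming row then gives 0.40 instead of 0.30, so one-sided adjustment can create bias. The week-1 comparison has 50 people per condition and variance 2(σ_b² + σ_w²)/50 = 0.04(σ_b² + σ_w²), where σ_b² is the between-person variance. That is at least 3 times the plain contrast.

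**The case against.** The strongest reply is that randomization, not the order factor, is the main control of priming, and that it works against the symmetric part. This stands: equal priming of both stand-alone weeks gives zero bias under balanced orders. A reader might infer that any priming between weeks passes directly into the STRIVE versus DISE estimate. The article does not support that, because it randomizes the weeks and gives no size or direction for priming. Nor is two-thirds of the carryover a general figure; it belongs to one assumed mechanism.

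A second reply is that a factor for order, in a condensed article, might include an order-by-condition interaction, which could detect and model carryover. That is possible in a fuller analysis plan, but the sentence does not say it, and the only interaction named is instrument by mode. The sentence as printed credits the term with a property that it lacks.

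Third, the planned model also uses the combined week, where both instruments cover the same days. If only DISE-only weeks are primed by 0.3 and the true difference is 0.30 in both modes, the combined-week contrast is unbiased. An instrument effect averaged over mode would then be (0.10 + 0.30)/2 = 0.20. This is fair, but the stand-alone comparison is one the design sets out to make, and there the estimate is 0.10.

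Finally, a full carryover model is expensive. This also stands, and is why it is not proposed as the main analysis.

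**Conclusion.** The point holds in a limited form. An order main effect leaves the within-person STRIVE versus DISE contrast unchanged, and a week-position term does not remove carryover, so the article's description of the adjustment is wrong as written. The consequence depends on priming being unequal between the two stand-alone weeks. With 6 equally used orders the bias is then one-third of the difference for preceding-week carryover, or two-thirds if any earlier use primes the stand-alone weeks unequally; with equal priming it is zero. Equal priming cannot be taken for granted, since logging events as they happen and completing an evening inventory are different tasks, but the article gives no evidence of inequality either. The set of orders, their balance and all carryover sizes are assumptions. This should be corrected before analysis, but it does not invalidate the design and is not a must-fix.

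**What to change.** 1. Do not describe the order main effect as accounting for carryover, and state the set of orders and how they are balanced.
2. Keep the randomized within-person contrast as the main analysis, with week (1, 2, 3) as a within-person factor.
3. Pre-state two sensitivity analyses: (a) a model with condition-specific prior-exposure terms for both the DISE-only and the STRIVE-only week, or equivalently targeted order-by-condition terms; and (b) a comparison of conditions in week 1 only, with about 50 people per condition if orders are balanced.
4. Say in advance that conclusions about stand-alone use will be qualified if these analyses differ from the main estimate.

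The cost is some analysis text and a little more analysis; data collection does not change. The prior-exposure model has about 5 times the variance of the main contrast (standard error about 2.2 times) and the week-1 comparison is also less precise. A difference from the main estimate must therefore be read with its interval, and neither should be made primary.
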